### Adverse event management and emergency termination of the study

Adverse events in this study include, but are not limited to, myocardial infarction, pulmonary embolism, and cerebrovascular disease. Patients will be closely monitored in the study period. If there are suspicions for any adverse event, the study team will discontinue the intervention and break the blind, and patients will be treated appropriately by surgeons and internal medicine physicians. Compensation will be offered to those who suffer harm from trial participation. All adverse events will be recorded and reported in the final manuscript. If patients refuse to participate at any time point during the study, the trial of related patients will be immediately terminated. Reasons of participants who discontinue and deviate from the trial should be recorded.

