## Methods

### Study design

This study is a clinical randomized controlled trial of estimated 130 patients with knee osteoarthritis undergoing TKA in Peking University Third Hospital (Fig. 1). All patients are randomly divided into the tourniquet group and non-tourniquet group (65 patients each). A tourniquet is applied throughout the surgery in the tourniquet group. In the non-tourniquet group, a tourniquet is tied up but will not be inflated. The trial aims to compare clinical outcomes of TKA with and without a tourniquet. Single binding is performed in this trial which means that the patients are unaware of whether the tourniquets are used in their surgeries. The study will stop once the enrollment is completed.

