### Allocation and randomization

All participants who met the study inclusion and exclusion criteria are randomly assigned in a 1:1 ratio to the tourniquet and non-tourniquet groups by the method of random envelope. Prior to study initiation, an independent statistician will use the SAS 9.4 software (SAS Inc., Cary, NC, USA) to generate a blocked random number sequence in permuted blocks of 4 participants. The electronic data capture system automatically generates participant ID numbers in sequence, which are subsequently linked to tourniquet assignments at randomization. Both the participants’ ID numbers and their allocation groups (tourniquet or non-tourniquet) will then be sealed in an envelope. The scientific secretory of this trial is responsible for enrolling participants and assigning participants to intervention (Table 1).

**Table 1 Tab1:** Schedule of enrollment, interventions, and assessments

Time point		Study period									
		Enrollment	Allocation	Post-allocation							
				t1	t2	t3	t4	t5	t6	t7	t8
Enrollment	Eligibility screen	X									
	Informed consent	X									
	Randomization		X								
Interventions	Tourniquet group				X						
	Non-tourniquet group				X						
Assessments	Demographic data			X							
	Quadriceps thickness			X			X				
	Quadriceps stiffness			X			X				
	Isokinetic muscle strength test								X		
	3D gait analysis								X		
	Posture stability testing								X		
	Thigh circumference			X		X	X				
	VAS score					X	X	X	X		
	Opioid consumption						X				
	Knee function score			X						X	X
	Postoperative satisfaction score									X	X
	Operation time				X						
	Intraoperative blood loss				X						
	Perioperative blood loss						X				
	Blood transfusion rate					X	X	X			
	d-dimer			X		X	X				
	C-reactive protein			X		X	X				
	Complications					X	X	X	X	X	X

*t1* before the operation, *t2* in operation, *t3* 1 day after the operation, *t4* 3 days after the operation, *t5* 2 weeks after the operation, *t6* 6 weeks after the operation, *t7* 3 months after the operation, *t8* 1 year after the operation

Participants and researchers who offer ultrasound and rehabilitation evaluation will all be blinded to the group allocation. However, in case of any medical emergency in the study period, allocation will be unblinded to researchers and clinicians for further medical treatment.

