### Baseline procedures

All patients are operated on by the same surgeon. This surgeon has more than 15 years of TKA experience including non-tourniquet TKA and operates at least 300 TKAs per year. All the surgeries are operated by conventional tools. Medial patellar skin incision, medial parapatellar arthrotomy, and measured resection are adopted in all patients. The patella is resurfaced and denervated by hand saw instead of patella replacement. Posterior stabilized implants (Legion from Smith and Nephew, Memphis, TN, USA) are selected.

Perioperative treatments are the same in both groups. Patients all receive intraspinal anesthesia or general anesthesia along with controlled hypotension which is defined as a reduction of the systolic blood pressure to less than 90 mmHg and a reduction of mean arterial pressure (MAP) to less than 65 mmHg or a 30 to 40% reduction of baseline MAP. Before the surgery, all the patients receive a single-time femoral nerve block instead of a continuous femoral nerve block to reduce postoperative pain. Tranexamic acid is used before skin cutting (1 g ivgtt) and before skin suture (1 g ivgtt). Thromboprophylaxis is done with sodium enoxyeparin, 4000 IU per day, starting 12 h after surgery. After the surgery, no femoral block tube or drainage tube is reserved.

Compression of elastic bandage to the surgery limb after suture (removed 24 h after surgery) and active and passive ankle pump training (start immediately after surgery) are adopted in both groups. No patients use continuous passive motion machine. Patients stay in a rest position with the knee in full extension, and they start active and passive rehabilitation training guided by a physical therapist 12–24 h after surgery (local ice compress for 15 min after each training). Patients are encouraged to perform isometric quadriceps exercise and walk with a walker on the first postoperative day. Range of motion (ROM) exercises are performed twice a day in the 6-week period. At 4–6 weeks after surgery, patients are encouraged to walk without aid gait.

The standard plan of postoperative analgesia is also the same in the two groups. Flurbiprofen Axetil (100 mg bid ivgtt) is regularly used for all patients for 2 days after surgery (patients with sulfonamides allergy use parecoxib sodium 40 mg bid ivgtt). If pain control is not satisfying, tramadol or oxycodone (1 tablet once, po) will be used.

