### Intervention

A tourniquet is tied to patients in both groups after anesthesia so that tourniquet application is blind to patients. Tourniquet in the tourniquet group is inflated to a standard pressure of (260 ± 10) mmHg (from skin cutting to skin suture). Tourniquet in the non-tourniquet group will not be inflated. There is no concomitant intervention in this study. Proper treatment and care of participants’ combined diseases are allowed. Extra use of analgesic, anticoagulant, and anti-anemia drugs out of the study protocol is prohibited. Participants will be excluded from the trial if these drugs are necessary.

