### Follow-up

Participants are followed up via study questionnaires at 2 weeks, 6 weeks, 3 months, and 12 months after surgery. In 2-week follow-up, the wound recovery, blood transfusion volume, and VAS score of the affected limb are recorded. In a 6-week follow-up, quadriceps function is evaluated by isokinetic muscle strength testing, three-dimensional gait analysis, and posture stability testing. KSS, WOMAC, and postoperative satisfaction score are recorded 3 and 12 months after surgery. Complications are recorded in every follow-up.

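### The article gives two different triggers for breaking the blind; the wider one, suspicion of any adverse event, puts blinding at avoidable risk

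*Protocol article*

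**What the plan says.** The section on adverse event management and emergency termination sets this rule: "If there are suspicions for any adverse event, the study team will discontinue the intervention and break the blind". It describes what counts in open terms: "Adverse events in this study include, but are not limited to, myocardial infarction, pulmonary embolism, and cerebrovascular disease". It does not say to whom the blind is broken.

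The section on allocation and randomization first states who is blinded. Participants are, and "researchers who offer ultrasound and rehabilitation evaluation will all be blinded to the group allocation". It then gives one exception: "in case of any medical emergency in the study period, allocation will be unblinded to researchers and clinicians for further medical treatment".

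Three other statements bear on the point:

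- Study design explains single blinding by saying that "the patients are unaware of whether the tourniquets are used in their surgeries".
- Intervention gives the inflation window and the control condition: "from skin cutting to skin suture). Tourniquet in the non-tourniquet group will not be inflated".
- Baseline procedures states: "All patients are operated on by the same surgeon".

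**The concern.** A team following the adverse event section would break the blind in cases where the allocation section would not. Nothing else in the article reconciles the two rules.

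The wider rule also suits this intervention poorly. A code break is justified when knowing the allocation changes what is done for the patient. Here the exposure is over once the wound is closed, and the person best placed to use the information already has it.

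What is at stake is mainly the patient's blinding. The control group wears an uninflated cuff for exactly that reason. Pain scores, WOMAC and satisfaction are reported by patients, some of them up to a year after surgery. The orthopedic researchers who collect them are not among those listed as blinded, so the patient's own blinding is the main stated protection for these outcomes. Assessor blinding could also be affected, because the allocation section refers to researchers without setting the assessors apart.

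**Working it through.** There is no figure in the plan to reproduce. The check is a comparison of the text, followed by an illustration of scale.

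**1. The two rules side by side**

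| | Allocation and randomization | Adverse event management |
|---|---|---|
| Trigger | Medical emergency | Suspicion of any adverse event |
| Scope | Emergencies during the study | Open list with three serious examples |
| Link to treatment | Stated as the purpose | Treatment follows, but is not a condition |
| Who is told | Researchers and clinicians | Not stated |

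A suspected event that is not an emergency meets the right-hand trigger and not the left-hand one. The rules therefore differ as written.

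**2. What the wider trigger adds to care**

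- The cuff is inflated only between incision and closure. After surgery there is no intervention left to stop.
- One surgeon performs every operation, is not listed as blinded, and will know whether the cuff was inflated.
- The adverse event section itself names surgeons among those who treat the event.

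For most postoperative events, a formal code break would therefore tell the treating side little that it could not already learn.

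**3. Which outcomes depend on the blind (Table 1 and Follow-up)**

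- Patient-reported: VAS at 1 day, 3 days, 2 weeks and 6 weeks. At the later visits, "KSS, WOMAC, and postoperative satisfaction score are recorded 3 and 12 months after surgery".
- Assessor-measured: thickness and stiffness at day 3; strength, gait and posture tests at 6 weeks.
- The primary outcome can be affected only by a break before the day-3 scan that also reaches the examiner. A thrombosis first found at that scan comes too late to unblind it.

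**4. Scale, on assumptions only**

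The article gives no event rate. Let *p* be the share of one arm (65 patients) that is unblinded and *d* the resulting shift in those patients. The between-group mean difference then moves by *p* × *d*. Both inputs are assumed: *p* = 2%, 10% or 30%; *d* = 1 VAS point, or 0.31 cm of thickness, which equals the whole non-inferiority margin.

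| *p* | Patients in one arm (65 × *p*) | VAS shift (*p* × 1) | Thickness shift (*p* × 0.31 cm) | Share of the 0.31 cm margin |
|---|---|---|---|---|
| 0.02 | 1.3 | 0.02 | 0.0062 cm | 2% |
| 0.10 | 6.5 | 0.10 | 0.031 cm | 10% |
| 0.30 | 19.5 | 0.30 | 0.093 cm | 30% |

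The thickness column is deliberately severe: it assumes that every unblinded patient in one arm is misread by the full margin, in the same direction. The planned primary test is Mann-Whitney, so a calculation on means shows scale only. None of these values estimates what will happen.

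**The case against.** The strongest case for the plan is that the adverse event section was meant narrowly. Its heading refers to emergency termination, its three examples are all grave, and its sentence ends with treatment by surgeons and physicians. Local problems such as bruising, hematoma and vesicles are called complications elsewhere and carry no unblinding instruction. Stopping the intervention makes good sense during surgery, when the cuff can be deflated. The allocation section also never says that an emergency is the only ground for unblinding. And a condensed article may leave the details of a code break to the full protocol.

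Much of this stands as a reading of intent. It does not remove the conflict. The operative words cover suspicion of any event, the list is expressly not closed, and the sentence is not confined to the operation. An emergency is the sole exception that the allocation section states. The point concerns two rules that are both written out, not a detail left for elsewhere.

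Three stronger readings are tempting and are not supported:

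- **That patients or assessors will be told.** The adverse event section names no recipient. The allocation section names researchers and clinicians, and its stated purpose points to treating staff. The risk to patients is inferred from the way the article defines its blind; the risk to assessors is only a possible reading.
- **That every minor local complication triggers a break, and more often in one arm.** The open list does not exclude such events, but it does not name them, and no rates are given.
- **That many late assessments are biased.** None is shown to be exposed. Patients who need extra anticoagulant are to be excluded from the trial, so some with a thromboembolic event may provide no later data, although the intention-to-treat analysis limits that point.

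**Conclusion.** The concern holds as a conflict between two stated triggers. Read literally, the adverse event section would break the blind in patients whose care does not need it, without saying who is told. That puts patient blinding, and possibly assessor blinding, at a risk that can easily be avoided.

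The size and direction of any bias are unknown, because the article gives neither an event rate nor a record of who would learn the allocation. A reader might infer that the primary comparison is compromised. The documents do not support that: the primary outcome is read at day 3 by an examiner stated to be blinded, and only an earlier break that reached this examiner could matter. The primary conclusion is unlikely to turn on this. It is a cheap improvement, not a flaw that threatens the trial.

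The conclusion rests on taking the adverse event sentence at its word and on the surgeon knowing whether the cuff was inflated, which follows from performing the operation.

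**What to change.** Put one rule in both sections:

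- The blind is broken only when knowing the allocation is needed for urgent care.
- The allocation is disclosed to the treating clinicians only. In the allocation section this replaces the reference to researchers and clinicians.
- The ultrasound examiner, the rehabilitation assessors, the statistician and, where possible, the patient stay blinded.
- All other adverse events are treated and recorded as already planned, without a code break.

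The cost is a wording change in two places, with no extra staff or visits. The downside is that unblinding is no longer automatic: a clinician who needs the allocation must ask for it. The Trial status section reports 84 patients recruited, so, on that count, an amendment would cover the remaining 130 − 84 = 46 patients and any follow-up not yet done in the others.

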### Outcomes and measures

#### Preoperative measurements

Demographic information of all the patients is collected, including gender, age, height, weight, and BMI. Baseline outcomes including quadriceps thickness and stiffness, thigh circumference, knee function scores, hematocrit and hemoglobin level, d-dimer, and C-reactive protein level in the serum are evaluated before surgery but after randomization and allocation.

#### Primary outcome

Bilateral lower extremity ultrasonography is performed before and 3 days after surgery to evaluate the thickness of the quadriceps muscle. The inspection is performed by a Canon Apilio I900 ultrasound with L18-5 probe. The probe is placed vertically on the body surface without compressing. The maximum distance from the front to the back of the quadriceps on the horizontal cross-section is selected as the quadriceps thickness; meanwhile, muscle echo and texture are observed. The ultrasound measurements are conducted by the same ultrasound examiner.

#### Secondary outcomes

##### Quadriceps stiffness

Quadriceps stiffness is also evaluated in lower extremity ultrasonography before and 3 days after surgery. With the method of shear wave elastography (SWE), the muscle shear wave propagation velocity (m/s) along the long and short axis in the same section is measured 5 times, and its median is taken as quadriceps stiffness. The occurrence of venous thrombosis is detected simultaneously.

##### Rehabilitation outcomes

It is difficult for end-osteoarthritis patients to accomplish tests of quadriceps function. Therefore, quadriceps function was assessed at 6 weeks postoperatively. Three tests including isokinetic muscle strength testing, three-dimensional gait analysis (3DGA), and posture stability testing are selected.
Isokinetic muscle strength test

The quadriceps muscle strength is evaluated using BIODEX’s multi-joint isometric training test system. All patients are tested by the same therapist to reduce operator bias in the trial. The instrument shall be systematically calibrated before the test, and the patients shall be informed of the methods and requirements of isometric test, but no warm-up exercises are performed. The non-operative limb is tested first to obtain basic reference data and then the operative limb. Outcomes include peak torque, peak torque/weight ratio, peak torque angle, total work, and average power.
b.Three-dimensional gait analysis

SMART-D 400 3D gait analysis system is used. Patients are asked to make 6 round trips with a natural gait, and the Smart Analyzer software is issued to calculate the spatial and temporal parameters and ankle kinematics parameters. Outcomes include stride time, standing time, swinging time, standing phase, swinging phase, leg support phase, stride length, step length, step speed, stride frequency, and angle change of hip, knee, and ankle when walking.
iii.Posture stability testing

Active Balancer EAB-100 is used for testing. Four static postures in different standing conditions are included: T1, sanding on a hard plate with eyes open; T2, standing on a hard plate with eyes closed; T3, standing on a sponge pad with eyes open; and T4, standing on the sponge with eyes closed. The test time for each condition is 30 s, and there is a rest of 3 min (sitting position) in two test intervals. The real-time movement of the center of plantar pressure is recorded, and the parameters related to its movement are analyzed by professional software. Outcomes include the total track length and average velocity of the displacement of the plantar pressure center.

##### Other secondary outcomes

Other secondary outcomes are also evaluated, including operation time, intraoperative and postoperative blood loss, blood transfusion rate, thigh circumference, VAS score, opioid consumption, d-dimer and C-reactive protein level in the serum, knee function score, postoperative satisfaction score, and complications.

Operation time, which also means tourniquet application time, is evaluated as well. It is defined as the time from skin cutting to the skin suture, and it is accurate to minutes.

Intraoperative blood loss and postoperative blood loss (3 days after surgery) are also evaluated in this trial. Hematocrit level is tested before surgery and 3 days after surgery. Calculating methods are as follows: intraoperative blood loss = intraoperative fluid intake volume + intraoperative irrigation volume + gauze infiltration volume (ml); postoperative blood loss = total blood loss − intraoperative blood loss; total blood loss is calculated by gross linear equation [15]: total blood loss=preoperative blood volume (PBV) ×(preoperative Hct – postoperative Hct)/average Hct, average Hct=(preoperative Hct + postoperative Hct)/2; preoperative blood volume is calculated by Nadler equation [16]: PBV = K1 × height (m)3 + K2× weight (kg) + K3 (for male: K1 = 0.3669, K2 = 0.03219, K3 = 0.6041; for female, K1 = 0.3561, K2 = 0.03308, K3 = 0.1833).

Blood transfusion and transfusion volume after surgery are recorded, and blood transfusion rate is calculated in 1 day, 3 days, and 2 weeks after surgery. Hemoglobin level is tested before surgery as well as 1 day and 3 days after surgery. Blood transfusion is done only if Hb level is lower than 70 g/L, or Hb level is between 70 and 90 g/L with symptoms of anemia like weakness and palpitations. The standard transfusion solution is 400 mL of suspended erythrocyte each time, with a reexamination of blood routine on the second morning.

The circumference of the upper third of the affected thigh is measured with a tape 1 day before surgery as well as 1 day and 3 days after surgery, with an accuracy of 0.1 cm. The swelling degree of quadriceps can be reflected by comparing the circumference in the two groups preoperatively and postoperatively.

VAS scores of the thigh and knee are separately evaluated at 1 day, 3 days, 2 weeks, and 6 weeks after surgery. Opioid consumption (in morphine equivalence) in 3 days after surgery is also recorded to further evaluate postoperative pain.

d-dimer and C-reactive protein (CRP) level in the serum is tested before surgery as well as 1 day and 3 days after surgery to reflect ischemia-reperfusion injury and inflammatory reaction. Complications of patients in both groups such as deep vein thrombosis, hematoma, and anemia are recorded at 2 weeks, 6 weeks, 3 months, and 12 months after surgery.

The knee function score KSS (Knee Society Score) and WOMAC (Western Ontario and McMaster Universities Osteoarthritis Index) are also evaluated before surgery as well as 3 months and 1 year after surgery. Both of the scores are widely used knee function scores worldwide. Their validity and reliability have been verified many times [17–22].

Postoperative satisfaction score is recorded 3 months and 1 year after surgery. It ranges from 1 to 5 points to reflect patients’ satisfaction rate of surgery and recovery. (1 = very dissatisfied, 2 = not satisfied, 3 = neutral, 4 = satisfied, 5 = very satisfied)

In addition, all complications such as deep venous thrombosis, skin vesicle, subcutaneous ecchymosis, and hematoma will be recorded in the study period.

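### The printed intraoperative blood-loss formula adds irrigation fluid as if it were blood, so intraoperative loss is overstated and postoperative loss, found by subtraction, is understated and can be negative

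*Protocol article*

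**What the plan says.** All the definitions are in the Protocol article, Other secondary outcomes.

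- Intraoperative loss: "intraoperative blood loss = intraoperative fluid intake volume + intraoperative irrigation volume + gauze infiltration volume (ml"). Three terms are added and none is subtracted.
- Postoperative loss: "postoperative blood loss = total blood loss − intraoperative blood loss".
- Total loss: "total blood loss=preoperative blood volume (PBV) ×(preoperative Hct – postoperative Hct)/average Hct", where average Hct is the mean of the two values.
- Blood volume (PBV) comes from height in metres and weight in kilograms, with coefficients "for male: K1 = 0.3669, K2 = 0.03219, K3 = 0.6041; for female, K1 = 0.3561, K2 = 0.03308, K3 = 0.1833".
- Sampling: "Hematocrit level is tested before surgery and 3 days after surgery".
- Transfusion: "Blood transfusion and transfusion volume after surgery are recorded, and blood transfusion rate is calculated in 1 day, 3 days, and 2 weeks after surgery". Also: "The standard transfusion solution is 400 mL of suspended erythrocyte each time".

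Intraoperative and postoperative blood loss are both listed as secondary outcomes. No other section of the article restates or corrects the formulas.

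**The concern.** Blood lost in theatre is normally what suction collects, less the irrigation fluid mixed into it, plus what the gauze holds. The printed formula gives irrigation a plus sign, and its first term names fluid intake, not suction. Whatever that term means, fluid that is not blood is counted as blood. Because postoperative loss is a remainder, the error passes into a second listed outcome with the opposite sign.

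Reduced intraoperative bleeding is the reason the Background gives for using a tourniquet, so readers will look at this comparison. If the formula is applied as printed, both outcomes will largely reflect fluid volumes, and some patients will have impossible values.

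A separate and smaller matter is that total loss rests on the fall in haematocrit to day 3. Red cells transfused before that sample raise the haematocrit and conceal loss. The formula has no term for them, although the volume is recorded.

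**Working it through.** The article gives no blood-loss figure to reproduce, so the printed formulas are evaluated directly. The formulas, PBV coefficients and 400 mL transfusion volume come from the article. Body sizes, haematocrits, fluid volumes and red-cell content are assumptions.

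**1. Total loss, assumed woman of 1.58 m and 65 kg**

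- PBV = 0.3561 × 1.58³ + 0.03308 × 65 + 0.1833 = 1.405 + 2.150 + 0.183 = 3.74. This makes sense only in litres, whereas the intraoperative formula is in mL.
- Hct 0.40 to 0.32: total loss = 3.74 × 0.08 / 0.36 = 0.83 L.
- With 1 L of irrigation and the other two intraoperative terms set to zero, postoperative loss = 0.83 − 1.00 = −0.17 L.

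**2. Size of the error under each reading of the first term**

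- *Suction volume, irrigation included.* Printed minus correct = (suction + irrigation + gauze) − (suction − irrigation + gauze) = 2 × irrigation.
- *Aspirated blood, already net of irrigation.* The excess is 1 × irrigation.
- *Fluid given to the patient.* The excess is irrigation + infused fluid − aspirated blood. This is at least the irrigation volume whenever more fluid is infused than blood aspirated. Aspirated blood is then not measured at all.

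**3. Numerical check**

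Two assumed patients: the woman above (PBV 3738 mL) and a man of 1.70 m and 75 kg (PBV 4821 mL). Preoperative Hct is 0.40 and gauze volume 50 mL. The first term is either 1000 mL infused, or suction holding 50 or 200 mL of blood plus all the irrigation.

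| Day-3 Hct | Total loss, woman | Total loss, man |
|---|---|---|
| 0.34 | 606 mL | 782 mL |
| 0.30 | 1068 mL | 1377 mL |
| 0.27 | 1451 mL | 1871 mL |

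| Irrigation | Printed intraoperative loss, infused reading | Printed intraoperative loss, suction reading (correct 100 to 250 mL) | Postoperative loss as derived |
|---|---|---|---|
| 500 mL | 1550 mL | 1100 to 1250 mL | negative in 11 of 18 cases |
| 1000 mL | 2050 mL | 2100 to 2250 mL | negative in 18 of 18 cases, −179 to −1644 mL |

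The 18 cases are 2 patients × 3 day-3 haematocrits × 3 first-term values. With irrigation subtracted (suction reading), the woman going from 0.40 to 0.30 has postoperative loss of 1068 − 250 = 818 mL to 1068 − 100 = 968 mL. The printed formula gives −1182 to −1032 mL at 1000 mL of irrigation.

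**4. Transfusion before the day-3 sample**

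Assume that one 400 mL unit has Hct 0.50 to 0.60 (200 to 240 mL of red cells) and that blood volume stays constant. In the woman, Hct rises by 200/3738 = 0.054 to 240/3738 = 0.064.

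| Hct before surgery to day 3, had there been no transfusion | Loss without transfusion | Formula after one unit | Hidden |
|---|---|---|---|
| 0.40 to 0.32 | 831 mL | 151 to 256 mL | 575 to 680 mL |
| 0.40 to 0.26 | 1586 mL | 782 to 906 mL | 680 to 803 mL |
| 0.38 to 0.24 | 1688 mL | 828 to 960 mL | 728 to 860 mL |

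For the man at 0.40 to 0.26, the hidden loss is 691 to 820 mL.

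The conversion matters. In the 0.38 to 0.24 case, adding the raw 400 mL gives 1228 to 1360 mL. Adding red-cell volume divided by the observed mean Hct (200/0.337 to 240/0.342) gives 1530 to 1554 mL, much closer to 1688 mL.

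**The case against.** The strongest reply is that the first term and the plus sign are translation slips for suction volume and a minus sign. Literal use would produce plainly negative results that the trial team would notice. That is plausible, so it cannot be said that the data collected so far are wrong. But the printed formula is the article's only definition, and it is wrong as it stands.

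A reader might infer that all three losses are wrong. The document does not support that. Total loss uses only blood volume and haematocrit and never the intraoperative formula. It is biased only in patients transfused before the day-3 sample, and the article gives no expected transfusion rate. The missing transfusion term is also partly an omission. The equation is taken from a cited source, and the full protocol or SAP may say how the recorded volume enters. It is therefore a secondary point.

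A reader might also infer a biased comparison between arms. Under the suction reading the excess is twice the irrigation in both arms, so it cancels from the mean difference if irrigation is equal on average. The article gives no irrigation or transfusion figures by arm, so bias is possible but not shown. Cancellation does not rescue the reported levels or the negative values. It also fails under the infused-fluid reading, where aspirated blood drops out of the comparison.

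Finally, these are supporting outcomes. The Discussion treats blood loss as a supplement to the quadriceps measures. The article states that transfusion volume is recorded, but not that suction, irrigation and gauze volumes are kept separately.

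**Conclusion.** The point stands for two listed secondary outcomes. As printed, intraoperative loss is overstated by twice the irrigation volume if the first term is suction volume. Under the other readings it is overstated by at least the irrigation volume, provided that, on the infused-fluid reading, more fluid is infused than blood aspirated. Postoperative loss is understated by the same amount. The direction does not depend on the assumed patients. Whether a value turns negative does: at 1000 mL of irrigation it did in every case tried, and at 500 mL in 11 of 18.

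The transfusion gap is lesser. It understates total loss, and postoperative loss with it, by roughly 0.6 to 0.9 L per 400 mL unit under the assumed red-cell content, and only in patients transfused before the day-3 haematocrit. The quadriceps endpoint, its non-inferiority margin and the sample size are not affected.

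**What to change.** 1. Replace the definition with: intraoperative loss = suction volume − irrigation volume + blood absorbed in gauze. State how the gauze content is measured.
2. Keep postoperative loss = total − intraoperative, and express PBV and every loss in the same unit (PBV in litres × 1000 to give mL).
3. Confirm that suction, irrigation and gauze volumes were stored separately for patients already enrolled (84 at the time of the article), then recompute both outcomes for them. If only the printed sum was kept, say so and report that intraoperative and postoperative loss cannot be recovered for those patients.
4. For total loss, add transfusion given up to the day-3 sample with a stated conversion, for example transfused red-cell volume divided by mean Hct, and state the assumed red-cell content of a unit. Alternatively, report this as a sensitivity analysis.

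Items 1 and 2 are text corrections. Item 3 costs a data check and a recalculation if the components exist. Item 4 needs the already recorded transfusion volume and its timing relative to the day-3 sample. No change to the design, primary analysis or sample size follows.
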